# The use of a risk assessment and decision support tool (CRISP) compared with usual care in general practice to increase risk-stratified colorectal cancer screening: study protocol for a randomised controlled trial

**DOI:** 10.1186/s13063-018-2764-7

**Published:** 2018-07-25

**Keywords:** Colorectal cancer screening, Risk-stratified screening, Precision medicine, Primary care, Risk assessment tool, Decision support, Faecal occult blood test, General practice, Precision screening

## Abstract

**Background:**

Australia and New Zealand have the highest incidence rates of colorectal cancer worldwide. In Australia there is significant unwarranted variation in colorectal cancer screening due to low uptake of the immunochemical faecal occult blood test, poor identification of individuals at increased risk of colorectal cancer, and over-referral of individuals at average risk for colonoscopy. Our pre-trial research has developed a novel Colorectal cancer RISk Prediction (CRISP) tool, which could be used to implement precision screening in primary care. This paper describes the protocol for a phase II multi-site individually randomised controlled trial of the CRISP tool in primary care.

**Methods:**

This trial aims to test whether a standardised consultation using the CRISP tool in general practice (the CRISP intervention) increases risk-appropriate colorectal cancer screening compared to control participants who receive standardised information on cancer prevention. Patients between 50 and 74 years old, attending an appointment with their general practitioner for any reason, will be invited into the trial. A total of 732 participants will be randomised to intervention or control arms using a computer-generated allocation sequence stratified by general practice. The primary outcome (risk-appropriate screening at 12 months) will be measured using baseline data for colorectal cancer risk and objective health service data to measure screening behaviour. Secondary outcomes will include participant cancer risk perception, anxiety, cancer worry, screening intentions and health service utilisation measured at 1, 6 and 12 months post randomisation.

**Discussion:**

This trial tests a systematic approach to implementing risk-stratified colorectal cancer screening in primary care, based on an individual’s absolute risk, using a state-of-the-art risk assessment tool. Trial results will be reported in 2020.

**Trial registration:**

Australian and New Zealand Clinical Trial Registry, ACTRN12616001573448p. Registered on 14 November 2016.

**Electronic supplementary material:**

The online version of this article (10.1186/s13063-018-2764-7) contains supplementary material, which is available to authorized users.

## Background

Colorectal cancer is the third most common cancer in men (746,000 cases in 2012, 10.0% of the total cancer cases) and the second in women (614,000 cases in 2012, 9.2% of the total cases) worldwide. There is a wide geographical variation in incidence of colorectal cancer worldwide, with the highest rates in Australia and New Zealand and the lowest in Western Africa [1]. Internationally, screening is recognised as an effective method to reduce the burden of colorectal cancer. Randomised controlled trials of faecal occult blood test (FOBT) screening have demonstrated a 15–33% reduction in colorectal cancer mortality [2–4]. Despite this, few countries have an organised screening programme, and those with highly organised population-based screening often have a low screening uptake [5].

### Colorectal cancer screening in Australia

In Australia, biennial immunochemical FOBT (iFOBT) screening from age 50 years has been shown to be cost-effective with an estimated cost ranging from AUD$17,192 to 53,883 per year of life saved [6]. In 2006, the Australian government began the phased roll-out of a population-based colorectal cancer screening programme using the iFOBT. From 2020, the National Bowel Cancer Screening Program (NBCSP) will be fully implemented, offering biennial screening to all eligible people. The NBCSP sends a free iFOBT kit in the mail to all Australians between 50 and 74 years old for them to self-complete and return for analysis. Positive test results are managed by the participant’s nominated general practitioner who organises a colonoscopic investigation. Participation rates in the NBCSP remain low, with only 39% of the 2.6 million people invited returning a completed kit [7]. According to the Australian Commission on Safety and Quality in Healthcare report, almost 600,000 colonoscopies were performed in 2013–14 [8] suggesting that some people may be having colonoscopic screening instead of completing the NBCSP screening kit.

Australian guidelines (both previous and recently updated guidelines) recommend that colonoscopic screening should only be offered to individuals at increased risk on the basis of their family history of colorectal cancer [9, 10]. In 2012, based on the 2005 Australian Guidelines risk criteria [10], it was estimated that for every 1 million Australians 50 years and older, 80,000 people at average risk were being over-screened with colonoscopy, while 29,000 people at increased risk were not having the required colonoscopy [11, 12].

### Risk-stratified screening

People are not at equal risk of colorectal cancer. While the average population lifetime risk of colorectal cancer is around 5%, there is a wide spectrum of risk with large proportions of the population actually below or above the “average” risk [13].

Colorectal cancer risk for the quarter of the population with the highest contribution of risk factors is 20 times greater than for those in the lowest quartile, and 90% of colorectal cancer occurs in those in the upper half of the population for these risk factors [13]. Australian guidelines recommend screening with an iFOBT for people at “average and slightly increased risk” and colonoscopy for those at “increased risk”. However, these guidelines rely only on age and family history and are limited in their ability to detect individuals at high risk [10]. Risk prediction models can provide estimates of colorectal cancer risk so that more expensive and higher risk preventive strategies, such as colonoscopy, can be targeted at those most likely to benefit [14, 15].

### What is the difference between a cancer risk prediction model and a cancer risk assessment tool?

Risk prediction models are mathematical algorithms which combine demographic, clinical, lifestyle and genetic factors to accurately determine future risk of developing colorectal cancer [16]. A risk assessment tool applies a risk prediction model and presents risk information in a way that will change the actions of patients and clinicians. Identifying an accurate risk prediction model is simply the first step. Translating a risk model into clinical practice requires a risk assessment tool that is easy to use in a clinic, can improve practice and is acceptable to clinicians and patients.

An Australian colorectal cancer risk prediction model was developed and validated using data from the Colon Cancer Family Registry (CCFR) and includes risk/protective factors: age, sex, body mass index (BMI), diet (red meat and fruit), smoking (pack-years), previous colorectal cancer screening (FOBT and/or colonoscopy), polyp detection, use of medication (including non-steroidal anti-inflammatories, hormone replacement therapy, calcium) and first-degree relatives with colorectal/endometrial/ovarian cancer and age of diagnosis [14].

The Colorectal cancer RISk Predictor (CRISP) tool is a web-based risk assessment tool [17] which calculates an individual’s absolute risk of developing colorectal cancer (presented as 5-year and lifetime risk) (Fig. 1) based on an analysis of the Colon Cancer Family Registry [18]. The CRISP tool presents the risk information using previously evaluated risk communication formats [19, 20], and provides clinical decision support about recommended screening (Fig. 2). A 2.5% 5-year absolute risk of colorectal cancer was set as the threshold for switching from recommending biennial FOBT testing to 5-yearly colonoscopy. This threshold was chosen to be consistent with the risk categories recommending colonoscopy in the current National Health and Medical Research Council (NHMRC) guidelines. The CRISP tool also identifies people with a family history suggestive of a rare inherited cancer syndrome (e.g. Lynch syndrome) and recommends referral to a family cancer clinic rather than providing screening advice.

**Fig. 1 Fig1:**
[figure not shown]
Screenshot of the CRISP tool with an example of a data entry screen. CRISP Colorectal cancer RISk Prediction

**Fig. 2 Fig2:**
[figure not shown]
Example of a patient report generated by the CRISP tool

The development and evaluation of the CRISP tool has been informed by the UK’s Medical Research Council Framework for the design and evaluation of complex interventions [21, 22]. The CRISP tool design was informed by a qualitative study involving 14 GPs who used a prototype version of the CRISP tool in simulated consultations [17]. The methods to communicate risk information were tested using a randomised vignette study with patients in general practice. This informed a selection of expected frequency trees and comparative risk graphs as the primary method of risk communication for patients at average and increased risk respectively [20].

This protocol is for a multi-site, individually randomised controlled trial to test a primary care-led model of risk-stratified colorectal cancer screening, using the CRISP tool. The aim is to increase iFOBT uptake and reduce inappropriate colonoscopic screening in average-risk people, and to increase colonoscopic screening in people identified at higher risk. Our trial procedures were piloted in two general practices involving 85 participants. The pilot study demonstrated feasibility of the recruitment and randomisation procedures, refined the content of the CRISP consultation and confirmed acceptability of collecting patient-reported outcome measures [23].

The study protocol adheres to the SPIRIT statement (Additional file 1) [24].

### Objectives

The primary objective of the CRISP trial is to determine whether the effect of a standardised consultation using the CRISP risk assessment tool in general practice, compared with the provision of generic cancer prevention information, increases the proportion of participants who undergo risk-appropriate colorectal cancer screening; that is, completion of the right screening test (iFOBT or colonoscopy) based on an individual’s absolute risk of colorectal cancer and the Australian Guidelines at the time [10]. The secondary objectives are: (1) to test the CRISP tool compared with generic cancer risk reduction information on participants’ level of colorectal cancer risk perception, general anxiety, cancer worry and cancer screening intentions; and (2) to evaluate the CRISP tool on health service utilisation and healthcare costs.

### Hypotheses

A standardised consultation using the CRISP tool in general practice will increase risk-appropriate screening compared with generic information about cancer prevention at 12-month follow-up.The CRISP tool will increase the accuracy of participants’ risk perception and their intentions for risk-appropriate screening without an adverse increase in cancer-specific anxiety after 1-month, 6-month and 12-month follow-up.

## Methods

### Participants, interventions and outcomes

#### Study setting

This is a multi-site individually randomised controlled trial (RCT) set in at least eight general practices (primary care practices) in Melbourne, Australia. General practices are purposively sampled from VicRen, the University of Melbourne practice-based research network which includes at least 200 general practices [25]. Practices are recruited from different areas in Melbourne to maximise the sociodemographic diversity of participants.

Participants are recruited from general practice waiting rooms prior to an appointment with their GP. General practices are eligible if they have at least 1000 active patients between 50 and 74 years old, at least three consenting doctors and a private room available for recruiting for at least 3 days per week.

Before starting recruitment in each general practice, the research team meet with the GPs and practice nurses to ensure they understand the expected clinical action in response to the CRISP tool-generated risk assessment reports, including how to respond to the participants in the control arm.

### Participants

Eligible participants for the trial are aged between 50 and 74 years old, which is consistent with the target population for the Australian NBCSP. Participants are able to read and write English and competent to give informed consent. Patients with a previous diagnosis of colorectal cancer are excluded as the CRISP tool is only designed for people who have never had colorectal cancer. Patients with recent rectal bleeding or inflammatory bowel disease are excluded and referred for assessment by their GP because they may require colonoscopy as a diagnostic rather than screening procedure. Patients with known Lynch syndrome, familial adenomatous polyposis or any other specific genetic predisposition for colorectal cancer, ascertained by a detailed family history of colorectal and other cancers, are excluded/family history of colorectal and other cancers, are excluded.

### Recruitment

Participants attending a GP consultation for any reason are recruited directly from the waiting room of general practices. Eligible patients between 50 and 74 years old, identified by reception staff from the daily appointment list, are approached consecutively in the waiting room by a research assistant (RA). If the patient is interested in the study and fulfils the initial criteria (age and appointment with a consenting GP), the RA takes them through to the CRISP research officer (RO) in a private room. The RO will discuss the trial and determine their eligibility. This method of recruitment and intervention delivery is designed to maximise accrual and reduce recruitment bias, a significant flaw in most of the previous trials of cancer risk assessment tools (Fig. 3) [26].

**Fig. 3 Fig3:**
[figure not shown]
Trial flow chart (refer to Fig. 4 data collected at each time point)

If the patient is eligible and interested, the RO explains the plain language statement and consents to the patient (Additional file 2). The participant is given a signed copy of the consent form for his/her records. The RO completes an online baseline questionnaire with the participant once he/she has consented to the study but prior to randomisation. The baseline questionnaire captures a specific clinic identification code and other response data, and these data are embedded into a clickable link at the conclusion of the survey. This link points to another server which hosts randomisation software. Randomisation is automated on completion of the online baseline questionnaire.

### Intervention arm

Delivery of the intervention occurs on the day of recruitment prior to the participant’s consultation with their GP. After completion of baseline data collection, those randomised to the intervention arm have their baseline data automatically uploaded into the CRISP tool. Using the risk calculation and risk-specific screening recommendations generated by the CRISP tool, the RO discusses the participant’s risk of colorectal cancer and recommendations about appropriate colorectal cancer screening using a standardised consultation script. A print-out summarising the participant’s colorectal cancer screening recommendations and risk is given to them to discuss with their GP (Fig. 2). The CRISP tool also generates a report for the GP which is subsequently uploaded into the participant’s electronic records. If the participant is classified by the CRISP tool to be at average risk and is due for an iFOBT (i.e. has not completed one in the previous 2 years), he/she is provided with a free iFOBT kit and asked to discuss this with his/her GP. The RO provides brief advice on how to complete the iFOBT kit. Those at increased risk who require a referral for colonoscopy are advised to discuss this with their GP. Participants who are given an iFOBT kit during the CRISP consultation receive a reminder by text message at 1 month to prompt them to complete their kit. The intervention arm participants also receive generic information on how they can reduce their colorectal cancer risk.

The core intervention is the CRISP consultation but the other components are designed to increase self-efficacy to complete the FOBT for those at average risk as part of an overall complex intervention [21, 22].

### Control arm

After completion of the online baseline data, participants randomised to the control arm are automatically directed to an electronic presentation of the Cancer Council Victoria’s *Cut Your Cancer Risk* brochure [27]. The RO discusses this with the participant using a standardised consultation script. The focus of the consultation involves explaining modifiable factors that can reduce the cancer risk including lifestyle changes, and brief information about the national cancer screening programmes for breast, cervical and colorectal cancer. This is designed as a credible attention control which also increases engagement in the trial for control participants to minimise attrition. All participants receive a hard copy of the brochure. Participants randomised to the control arm continue to access health services as “usual care”.

### Random allocation, concealment mechanism and blinding

Random allocation of the participant to either the intervention or control arm is automated on completion of the online baseline questionnaire to ensure allocation concealment. The random allocation sequence, stratified by general practice, was computer-generated by our statistician (PC) with a 1:1 allocation ratio using random permuted block sizes of four, six and eight within each stratum. This sequence is incorporated into the randomisation software. Within each clinic (stratum), the randomisation software allocates the randomisation code sequentially and then redirects the browser to the CRISP Web App if the participant is randomised to the intervention arm, or to a series of screens with the Cancer Council Victoria’s *Cut Your Cancer Risk* information [27] if randomised to the control arm.

### Data collected

Baseline data collected include: demographics (age, sex, postcode, language spoken at home and country of birth, marital status, highest education level attained) and clinical variables (age, height, weight, number of first-degree relatives with colorectal cancer and ages of diagnoses, smoking history, current fruit and red meat consumption, history of use of non-steroidal anti-inflammatory drugs, current use of hormone replacement therapy (women only) and calcium supplements, and history and clinical outcomes of previous FOBT, colonoscopy including previous polyps) [15]. Additional baseline measures of CRC risk perception [28, 29], generalised anxiety [30], cancer worry [31, 32] and intention to screen [33] are also included in the baseline questionnaire.

Health service use is tracked using data extracted from the Australian Government Department of Health Medicare Benefits Schedule (MBS) [34] that maintains information about visits to healthcare providers and diagnostic tests, the National Bowel Cancer Screening data to access FOBT screening and the Victorian Hospital Admitted Episodes Dataset (VAED) to access privately funded colonoscopic screening.

### Outcome measures

The primary outcome is the proportion of participants who have had risk-appropriate colorectal cancer screening measured at 12-month follow-up. For participants in the intervention arm, appropriateness of screening will be determined by the CRISP tool and is based on the participant’s 5-year absolute risk of colorectal cancer, using the 2.5% threshold, and their concordance with the recommended mode and frequency of screening. For the participants in the control arm, family history and previous screening data collected in the baseline questionnaire will be used to determine risk-appropriate screening in accordance with National Guidelines at the time of recruitment.

The CRISP tool was developed using the previous 2005 Australian guidelines which were revised in October 2017. As our trial was already underway with more than 300 participants recruited, the Trial Steering Committee agreed that it was not appropriate to change the recommendations halfway through recruitment. Nonetheless, the changes to the risk criteria in the revised guidelines were relatively minor but their potential impact will be examined in a pre-planned sensitivity analysis (see later) [9].

Screening behaviour will be obtained for all of the participants from the following sources: participant self-report; data from GP records (results of FOBT and/or colonoscopy); Medicare Benefits Schedule through the Department of Human Services (for specific colonoscopy item numbers); the National Bowel Cancer Screening Program; and the Victorian Admitted Episodes Dataset (for colonoscopies conducted in Victorian public hospitals not captured by MBS data).

The data collection will be done systematically and we will use a hierarchical approach to determine the final screening behaviour with self-report at the bottom of the hierarchy. Where possible, self-report will be validated from other data sources. The Steering Committee have formed a clinical sub-committee to make decisions about “appropriate screening” behaviour for discordant reported screening behaviour from the multiple data sources. Blinded clinical review will be conducted on a case-by-case basis to reach consensus when there are discordant results.

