A sensitivity analysis will also be conducted to assess the impact of using the revised 2017 Australian Colorectal Screening guidelines on the proportion of participants classified as having risk-appropriate colorectal cancer screening at 12 months and 5 years. All randomised participants will be included in the analysis in their assigned study arms in accordance with the intention-to-treat principle [39]. Possible differential attrition will be assessed by comparing baseline characteristics of those who withdraw against those who remain in the study. Appropriate methods for dealing with missing data will be detailed in the statistical analysis plan and be informed by a blinded review of the data. Sensitivity analysis will be used to assess the robustness of the missing data assumption.

A health economic analysis will combine a within-trial and modelled analysis of the cost-effectiveness of implementing the CRISP tool. The within-trial analysis will focus on the incremental cost per appropriately screened individual for the CRISP tool versus usual care. The modelled analysis will combine observed colorectal cancer detection rates from the trial with data from the published literature to investigate the longer-term cost-effectiveness of the CRISP tool using an economic model. Within-trial costs in the two study arms will be estimated based on data observed from general practice, MBS, the NBCSP and the VAED records. Mean estimates of costs will be used and confidence intervals will be generated by resampling (boot-strap) techniques. Benefits in the modelled analysis will be assessed as quality-adjusted life years (QALYs) by extrapolating the observed cancer detection rates from the trial to longer-term survival and adjusting them by published quality of life (utility) weights. Results will be presented in terms of the incremental cost-effectiveness ratio (ICER) as a cost per case detected for the within-trial period, and a cost/QALY gained for the modelled analysis. Sensitivity analyses will be conducted to test the robustness of the results of the economic analysis to variations in the underlying assumptions and inputs.

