### Blinding

The nature of the intervention means that participants cannot be blinded to their treatment allocation. GPs will only be aware of participants allocated to the intervention arm and will not be informed when a participant is allocated to the control arm. The majority of follow-up questionnaires will be completed by participants online or via post and those completed by telephone are done so with a blinded researcher. For the extraction of health service utilisation data, research staff will be blinded to allocation assignment. All study analyses will be conducted by a statistician blind to the participants’ study arm allocation; study arm allocation will be coded as A or B when data are extracted from the online databases and supplied to the statistician, with the key for the intervention or control arm revealed after data are analysed and interpreted. Investigators will also remain blind to the study arm allocation when interpreting the results.

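### The primary outcome is scored by the CRISP absolute-risk rule in the intervention arm and by the guideline family-history rule in the control arm, so the arms can differ even when screening behaviour is identical

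*Protocol article*

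**What the plan says.** The Outcome measures section of the protocol article defines success separately by arm. "For participants in the intervention arm, appropriateness of screening will be determined by the CRISP tool"; this uses 5-year absolute risk with the 2.5% cut-point, plus agreement with the recommended test and interval. The control arm has a different basis: "For the participants in the control arm, family history and previous screening data collected in the baseline questionnaire will be used to determine risk-appropriate screening", judged against the national guidelines in force at recruitment.

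The Background describes the two classifiers. For CRISP, "A 2.5% 5-year absolute risk of colorectal cancer was set as the threshold for switching from recommending biennial FOBT testing to 5-yearly colonoscopy". Its model also takes in BMI, diet, smoking, medication, polyps and earlier screening. Of the guidelines, the section on risk-stratified screening says that "these guidelines rely only on age and family history and are limited in their ability to detect individuals at high risk".

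The Objectives section names a single criterion for everyone, which combines absolute risk with the Australian guidelines. Statistical methods compares the arms' proportions at 12 months by logistic regression with general practice as a covariate. It repeats this at 5 years, and the economic analysis uses cost per appropriately screened individual.

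**The concern.** Randomisation makes the arms alike in baseline risk and prior screening. It does not protect a comparison in which the measuring rule itself depends on the arm.

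Take a participant with a CRISP risk of 2.5% or more and no qualifying family history. If that person has a colonoscopy, it counts as risk-appropriate in the intervention arm and as over-screening in the control arm. If the same person completes an iFOBT, the scoring reverses.

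The odds ratio therefore mixes any effect on behaviour with a difference in scoring. The hypothesis tested is no longer that of no change in behaviour. The 5-year outcome and the cost per appropriately screened individual inherit the same definition.

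**Working it through.** **1. Reproduce the design figure.** Inputs from Table 1 and the revised sample size section: 35% vs 25%, 80% power, two-sided 5%, 10% attrition.

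n = [1.960 × √(2 × 0.30 × 0.70) + 0.8416 × √(0.35 × 0.65 + 0.25 × 0.75)]² / 0.10²
= [1.2702 + 0.5422]² / 0.01 = 328.5, so 329 per arm.

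With attrition, 329 / 0.90 = 365.6, so 366 per arm and 732 in total. This matches the article, and power at 329 per arm is 80.1%. The arithmetic is sound, but it treats the whole 10-point difference as behavioural.

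**2. Express the artefact.** Let q be the share of participants to whom the two rules assign different recommendations. Among them, let a be the proportion meeting the CRISP recommendation and b the proportion meeting the guideline recommendation. With identical behaviour in both arms, the expected difference is

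D = q × (a − b).

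D is zero only if the rules never disagree (q = 0) or if, among those classified differently, the two success rates happen to be equal.

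**3. Choose a range.** The documents give none of q, a or b. Assumption, for illustration only: q = 5%, 10% or 15%, with a net gap a − b of 30 points in one direction. Then D = 1.5, 3.0 or 4.5 points. The nearest figure in the article is the 6.5% prevalence of increased risk (Sample size and power calculation). That is not a disagreement rate, so it neither confirms nor caps q. Used as a scale, it gives 0.065 × 30 = 1.95 points.

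**4. Type I error with identical behaviour.** SE = √(2 × 0.25 × 0.75 / 329) = 0.0338. The two-sided rejection probability is P(Z > 1.96 − D/SE) + P(Z < −1.96 − D/SE).

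| Net artefact D | D/SE | Rejection probability |
|---|---|---|
| 0 | 0 | 5.0% |
| 1.5 points | 0.44 | 7.3% |
| 1.95 points | 0.58 | about 9% |
| 3.0 points | 0.89 | 14.4% |
| 4.5 points | 1.33 | 26.6% |

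Using the separate variance of each arm instead gives 14.0% (upward shift) or 14.8% (downward shift) at 3 points, which is essentially the same.

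**5. Power if the artefact runs against the intervention.** The true effect is 35% vs 25%, with the observed intervention rate lowered by D. At D = 3 points (32% vs 25%), the critical difference is 1.96 × √(2 × 0.285 × 0.715 / 329) = 0.0690. The SE is √((0.32 × 0.68 + 0.25 × 0.75) / 329) = 0.0351. Power = P(Z > (0.0690 − 0.0700) / 0.0351) = 51.2%. The same calculation gives 71.7% at 1 point and 30.0% at 5 points.

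**6. After the fix.** With one rule in both arms, D = 0. Type I error is 5.0%. Power stays at 80.1% with 329 per arm, provided the 25% and 35% rates hold under the chosen rule.

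Steps 4 and 5 use a simple two-proportion test and ignore the practice covariate.

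**The case against.** The best defence is that the article chose the 2.5% threshold to agree with the guideline categories for colonoscopy, and built CRISP on the 2005 guidelines. This is relevant to how often the rules disagree, and the disagreement may be small. It does not remove the problem. It aligns a cut-point, not the classification of each person, and the case for CRISP rests on identifying people the guidelines miss.

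A second objection is that the magnitudes are assumed. That stands. The 30-point gap is applied in one direction throughout. Disagreement in both directions would partly cancel, and 27% is the worst corner of the grid.

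A reader might infer three stronger points, which the documents do not support.

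- **Blinding is contradicted.** The article says "study arm allocation will be coded as A or B when data are extracted", and discordant cases go to blinded clinical review. That review mainly settles conflicts between data sources about which test was done, which does not need the arm. A program or data manager could apply the arm-specific rule before the coded file reaches the statistician. This is a tension, not a contradiction.
- **The 2017-guideline sensitivity analysis reclassifies controls only.** Its stated purpose is "to assess the impact of using the revised 2017 Australian Colorectal Screening guidelines" on the proportion classified as appropriately screened, with no restriction to one arm. It can be read as covering everyone. The text should say which is meant.
- **People flagged for a family cancer clinic have no outcome rule.** For them CRISP "recommends referral to a family cancer clinic rather than providing screening advice". Known genetic predisposition is already an exclusion and the article calls the syndromes rare, so few should remain. How to score them is ordinary analysis-plan detail.

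**Conclusion.** The definition of the primary outcome is wrong as written and must be changed before analysis. Two participants with the same baseline data and the same screening can be scored differently because of their arm alone, and no stated analysis clearly scores both arms by one rule.

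That the asymmetry exists follows directly from the text. Its size and direction cannot be derived from the documents. The figures of about 7%, 14% and 27% for type I error, and the loss of power, are illustrations that depend on the assumed disagreement share and a one-directional gap. It would be going too far to say that the trial result will be biased by a material amount, or that it will favour the intervention. What can be said is that, under the present definition, readers could not separate a scoring difference from a change in behaviour.

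**What to change.** - Score every participant in both arms by one common, pre-specified rule for the primary outcome. Do the same for the 5-year outcome and for the cost per appropriately screened individual.
- Apply the other rule to both arms as a sensitivity analysis.
- State that the 2017-guideline sensitivity analysis covers both arms, and name the guideline edition used for scoring.
- Derive the outcome without the arm code, which a common rule makes possible.

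Either rule can be primary, but the choice has a small downside that should be stated. CRISP scoring in both arms judges controls by a standard that neither they nor their GPs could see. Guideline scoring in both arms judges intervention participants by a rule other than the advice they were given. Both common-rule results should therefore be reported.

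The cost is revised wording in the protocol and analysis plan, plus a batch CRISP calculation for controls. The inputs come from the baseline questionnaire, which every participant completes before randomisation. No new data, extra participants or change to the consultations are needed.
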